### Recruitment

All eligible GP-practices located within the predefined districts will be contacted by the HÄVG (*Hausärztliche Vertragsgemeinschaft,* HÄVG, the organisation that manages the GP-centred care contracts for the German Association of General Practitioners) via fax or on other communication channels such as newsletters and in continuing education workshops. If interested in participation, GPs and VERAHs sign up for the training described above. During the training they will receive detailed information about the study and sign the informed consent form.

Participating practices as study sites will check the inclusion criteria for a) patients with a planned hospital admission and b) patients after discharge after an unplanned hospital stay, provide the study information, and receive the signed informed consent forms which remain at the study site.

For the recruitment of the control group for the patient survey, GP-practices outside the intervention region will check the inclusion criteria for patients after hospital discharge. They hand out the patient survey questionnaire to eligible patients. Patients give their consent by filling in the anonymous questionnaire. Controls for the patient survey are recruited by GP-practices outside the intervention region.

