### Intervention group

The VESPEERA programme comprises recommended practices regarding discharge and care management, which is reinforced by laws (§ 11 Abs. 4 SGB V, § 39 Abs. 1a SGB V, § 112 Abs. 2, Satz 5 SGB V). The planned intervention picks up these regulations for optimal care and offers suggestions for their implementation and enhancement. Patients will not be randomly assigned to a study arm, but receive different intervention components based on the point of study enrolment and the patient’s medical need (see Table 1 – adjusted SPIRIT figure).

**Table 1 Tab1:** Intervention components for all study arms

Interventions		*Study arm 1:*planned admission into a participating hospital	*Study arm 2:*planned admission into a non-participating hospital	*Study arm 3:*unplanned admission into a participating hospital	*Study arm 4:* unplanned admission into a non-participating hospital	*Study arm 5:* control group, not participating in VESPEERA
GP-practice	Interventions in the GP-practice before admission: (A) assessment for admission (B) admission letter and patient brochure	X	X			
Hospital	Interventions in the hospital: (C) telephonic discharge conversation (D) determination of HOSPITAL-Score and patient discharge information	X				
GP-practice	Interventions in the general practice after discharge: (E) assessment for planning of follow-up care (F) telephone monitoring, depending on the risk for rehospitalisation	X	X	X	X	

Assessment for Admission (A): Before a planned hospital admission, the VERAH collects patient information on basic data, admission diagnosis, medical history, existing prescriptions, medication plans and other medical information, social, living and legal situation, communication and care needs.

Admission letter and accompanying patient brochure (B): Based on the assessment for admission, an admission letter which also specifies how and when the practice is available by phone for the hospital staff is created. Patients receive a brochure that informs and prepares for the hospital stay.

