Telephonic discharge conversation between GP-practices and hospital (C): For patients with complex interventions, medications or post-hospital care needs, a structured telephonic discharge conversation supports cross-sectoral exchange of information and clarification of responsibilities between the participating hospital and the responsible GP. In case of need, the AOK can be contacted to support the discharge process for example by providing medical products/ devices etc. in time.

Determination of HOSPITAL Score and patient discharge information (D): The participating hospitals collect data to determine the HOSPITAL Score, a score that indicates the risk for rehospitalisation within 30 days after discharge [14]. The score is communicated to the GP via the discharge letter. At the time of discharge, the patient receives patient discharge information, which summarizes the documents that the patient receives, follow-up care and appointments after discharge as well as different contact persons according to the respective care needs.

Assessment for planning of follow-up care (E): After hospital discharge, the patient has an appointment in the GP-practice (in case of need: home visit) with the VERAH. They conduct an assessment to determine the patients’ need for follow-up treatment and care. The GP receives a summary of the assessment, disclosing the patients’ care needs. Then, follow-up appointments, prescriptions and applications (such as rehabilitation or home care) can be determined and recorded. The patient receives a short summary of the arranged follow-up care plan. Based on the HOSPITAL Score, the GP determines the patients’ enrolment into the follow-up telephone monitoring. Patients with an intermediate or high risk for rehospitalisation, according to the HOSPITAL Score, should be enrolled in the follow-up telephone monitoring. For patients treated in a non-participating hospital, GP-practices have the option to gather data to determine the HOSPITAL Score. All data necessary to determine the score can be extracted from the discharge letter.

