### Control group

Using propensity score matching a control group from non-participating HzV-GP-practices in non-participating districts is built. Using claims-based data, age, gender, practice size and length of enrolment in GP-centred care and the district are considered to build the control group on practice level; to build a patient control group, age, gender, indication group and Charlson Comorbidity Index are used. Patients in the control group are not participating in the study and do not receive any intervention components.

The control group for the patient survey comprises patients that from approx. 50 comparable HzV-practices outside the intervention region. The inclusion criteria of the intervention group apply for patients of the control group.

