### Outcomes

The primary outcome is the number of rehospitalisations due to the same indication (three-digit ICD-10-GM code) within a time frame of 3 months (90 days) to the outpatient sector. This outcome is collected from claims-data on a case level, meaning that each patient can have more than one rehospitalisation, whereof all are considered in the analyses.

The following indicators have been defined as secondary outcomes and are based on pseudonymised claims-data, data collected within the CareCockpit software in GP-practices as well as patient survey data:number of rehospitalisations due to the same indication (three-digit ICD-10-GM code) within a time frame of 30 daysnumber of hospitalisations due to ambulatory care-sensitive conditions [17]number of patients discharged to the outpatient sector from a participating hospital where the prescription of medication is delayed [18]number of patients discharged to the outpatient sector from a participating hospital where referral to other health practitioner/s (*Heilmittel*) is delayednumber of patients discharged to the outpatient sector from a participating hospital where prescription for medical products/devices (*Hilfsmittel*) is delayednumber of patients discharged from a participating hospital who use emergency or rescue services (emergency medical service (*Ärztlicher Bereitschaftsdienst*), emergency ambulance (Notarztwagen), ambulance emergency response vehicle (*Notarzteinsatzfahrzeug*), ambulance, rescue helicopter (*Primärtransport – Luft*) within a time frame of 3 monthsaverage care cost per year and patient participating in the VESPEERA programmepatient-reported experiences and health-related outcome of cross-sectoral care using the German version of the instrument Patients’ Experiences Across Health Care Sectors (PEACS) [16]health-related quality of life, using the instrument EuroQol (EQ-5D) [19].

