### Sample size calculation

Since large-scale implementation of the VESPEERA program in a geographical region was intended, the number of participating GPs and hospitals was not restricted. Based on the number of GP-practices who participate in HzV-Care and the number of GP-practices who participate in the PraCMan programme, a number of 115 GP-practices are expected to participate. An estimation of the patient sample size was made using claims-data and several assumptions for hospitalisation rates, rates for planned and unplanned admissions, rates of patients with a high risk of rehospitalisation as well as drop-out rates. Assumptions were made based on analyses of AOK claims-data. Admissions are expected to be planned and unplanned in 50% of the cases, respectively. 56% of planned admissions are made by a GP and therefore can be included in the VESPEERA programme. 40% of planned admissions are cases that are expected to be treated in a participating hospital department. After discharge, we calculated with a 20% drop-out rate for patients who are transferred into a nursing home, who pass away or who do not seek GP contact after discharge. 60% of discharged patients are expected to have a risk of rehospitalisation (HOSPITAL Score indicating an intermediate or high risk for rehospitalisation). Figure 2 gives an overview on the sample sizes in each study arm. Given the estimated sample size, we can estimate the effect size (based on the hospitalisation rates after the intervention) that can be detected. Based on claims-data different numbers of hospitalisations can be expected for each of the intervention groups. The alpha level is set to 5%. The following power considerations are based on chi square tests (to test for group differences) and adjusted for the hierarchical structure of the data. The implemented models in the primary analysis will most likely lead to even higher power values. However, we consider the hierarchical structure of the data with cases nested in patients nested in hospitals or practices, respectively. A relatively high ICC (0.3) can be expected when considering measurements within patients, however the number of cases per patient will be relatively small (approx. 1.6 cases per patient). The clustering by hospitals or practices is taken into account with an expected number of approx. 540 patients per hospital and a presumed ICC of 0.03, which is a realistic value in health services research [20]. Furthermore, we assume a rate of re-hospitalisations of 23% in the control group. With a power of 80%, the following reductions in each of the intervention groups can be shown: For study arm 1 a sample size of 1905 cases can be expected. Hereby, a reduction of approx. 8% (from 23% to approx. 15%) can be shown. The control group will be matched and, therefore, the sample size will be the same. For study arm 2 when compared to the control group, the same reduction is detectable, as the same number of cases can be expected as in study arm 1. In a last step, both the study arms 3 and 4 are compared to the control group using a level of significance of 2.5%. In study arm 3, we expect a sample size of 3266 and, thus, a reduction of approx. 7% (from 23 to 16%) can be shown. In study arm 4, a sample size of 4899 hospitalizations can be expected which allows to show a reduction of approx. 6% (from 23 to 17%).

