#### Analysis sets

The primary analysis will be based on the intention-to-treat sample. This means that, in the analysis, patients will be considered in the treatment arm they were assigned to even if, for instance, not all interventions that were planned in this arm were delivered. In sensitivity analyses, the per-protocol set will be analyzed where these patients will be omitted. Patient to be excluded in this set will be defined before the analysis is performed. In a further as-treated-set the omitted patients will be included again but assigned to the treatment arm that describes best the treatment they actually received.

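### Arms 3 and 4 enrol index stays only at the GP visit after discharge, while claims controls carry no matching condition, so early rehospitalisations bias these two comparisons towards benefit

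*Protocol article*

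**What the plan says.** All of this is in the protocol article.

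- **Entry to the arms (Intervention group).** "Patients will not be randomly assigned to a study arm, but receive different intervention components based on the point of study enrolment". In Table 1, arms 3 and 4 receive only the post-discharge practice components, E and F.
- **Who recruits, and when (Recruitment).** Practices check and consent two kinds of patient: those with a planned admission, and "b) patients after discharge after an unplanned hospital stay, provide the study information, and receive the signed informed consent forms".
- **Start of the intervention in arms 3 and 4 (Intervention group, component E).** "After hospital discharge, the patient has an appointment in the GP-practice (in case of need: home visit) with the VERAH". No day is fixed for this visit.
- **Controls (Control group).** Patient-level matching uses age, gender, indication group and the Charlson index. "Patients in the control group are not participating in the study and do not receive any intervention components". So controls have no enrolment step.
- **Outcome (Outcomes).** Rehospitalisation for the same indication is counted "within a time frame of 3 months (90 days) to the outpatient sector". The sentence is incomplete, but the anchor can only sensibly be discharge. "This outcome is collected from claims-data on a case level, meaning that each patient can have more than one rehospitalisation".
- **Model (Primary analysis).** A difference-in-difference logistic mixed model for each arm against controls, adjusted for hospital service level and location. The rest is left to the matching.
- **Planning figures (Sample size calculation).** 23% in controls. Arm 3: 3266 cases, 23% to 16%. Arm 4: 4899 cases, 23% to 17%. About 1.6 cases per patient. A 20% loss after discharge for patients "who are transferred into a nursing home, who pass away or who do not seek GP contact after discharge".

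**The concern.** The two groups do not start at the same point. An index stay can be in arm 3 or 4 only if the patient got from discharge to the GP visit. A patient readmitted in that interval is unlikely to be enrolled for that stay, whereas the same course in a control is an outcome event. This is immortal time combined with selection on reaching the GP.

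The plan did align entry elsewhere: survey controls are patients who come to a GP practice after a hospital stay. The primary claims comparison has no counterpart.

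Nothing stated removes the problem. The model covariates do not bear on it. Intention-to-treat covers only patients already assigned to an arm. Difference-in-difference would cancel it only if the intervention group's pre-period cases carried the same GP-contact condition, and the article does not say that they do.

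Arms 3 and 4 are confirmatory comparisons and hold 3266 + 4899 = 8165 of the 11,975 planned cases (2 × 1905 + 8165). The Discussion looks ahead to area-wide implementation, so a false benefit here would matter.

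**Working it through.** **1. The plan's own figures, as yardstick.** With a pooled chi-square test, 80% power and 2.5% two-sided (sidedness is not stated), 23% against 16% needs 608 cases per group and 23% against 17% needs 844, before clustering. The planned 3266 and 4899 then imply design effects of 3266/608 = 5.4 and 4899/844 = 5.8. The stated hospital inputs give 1 + 539 × 0.03 = 17.17, so the detectable effects could not be reproduced. That is a separate matter. The 7 and 6 points serve here only as a measure of size.

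**2. Apparent rate with no treatment effect.**
- From the plan: 90-day risk 23%, so the cumulative hazard is −ln(0.77) = 0.2614.
- Assumed: a GP visit on day d = 3, 7 or 14, and a Weibull hazard with shape k = 1 (constant) or 0.7 (front-loaded).
- Risk before the visit: p = 1 − exp(−0.2614 × (d/90)^k).
- Rate in index stays that reach the visit without readmission: (0.23 − p)/(1 − p).

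| Shape k | Day d | p | Apparent rate | Spurious reduction (points) |
|---|---|---|---|---|
| 1 | 3 | 0.9% | 22.3% | 0.7 |
| 1 | 7 | 2.0% | 21.4% | 1.6 |
| 1 | 14 | 4.0% | 19.8% | 3.2 |
| 0.7 | 3 | 2.4% | 21.1% | 1.9 |
| 0.7 | 7 | 4.3% | 19.6% | 3.4 |
| 0.7 | 14 | 6.9% | 17.3% | 5.7 |

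The range of 0.7 to 5.7 points is 10–81% of arm 3's 7 points and 11–94% of arm 4's 6 points.

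**3. Dilution by later stays.** Later stays of an enrolled patient do not depend on a further enrolment visit. If only the first of 1.6 cases is affected, multiply by 1/1.6 = 0.625: 0.67 × 0.625 = 0.4 and 5.67 × 0.625 = 3.5 points. On that basis about 8165/1.6 ≈ 5100 stays carry the problem, not all 8165.

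**4. Chance of a false finding of benefit.** This uses 608 and 844 as effective sizes, supposes that the arm 3 and 4 tests are reached, treats each as a simple two-group comparison, and assumes that difference-in-difference cancels nothing. The nominal chance in this direction is 1.25%. With a visit on day 7, shape 1 to 0.7:
- All cases affected: 6–22% (arm 3), 7–30% (arm 4).
- Index stays only: 3–9% (arm 3), 4–12% (arm 4).

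**The case against.** Much of the case against limits the point without removing it.

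- **Controls' time zero is inferred.** The outcome sentence is incomplete, and an article may leave index-date rules to a fuller document. This stands as a caveat. But the recruitment point and the matching variables are stated here, and together they create the mismatch. If the 90 days ran from enrolment in the intervention arms, a constant hazard would give no bias, but a front-loaded one still would.
- **The pre-period group is not described.** A reader might infer that difference-in-difference certainly fails. The documents do not say who forms the before group, so that cannot be asserted. Cancellation is equally unstated.
- **Early events are not absent from arms 3 and 4 altogether.** Freedom from readmission is not an eligibility criterion. A patient readmitted early may enrol after the second stay, and all later rehospitalisations count. The bias belongs to the index stay.
- **Day 14 is towards the upper end.** The first monitoring call should fall within two weeks of discharge and follows assessment E, so for monitored patients the visit should usually come earlier.
- **Direction is not wholly one-sided.** Early deaths among controls prevent readmission and offset part of the bias.

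Two further inferences are unsupported. One is that losing nursing-home and no-contact patients adds to the bias. Patients who do not seek the GP may be those who recovered well, and the 20% is stated for discharged patients generally, not as an enrolment loss in arms 3 and 4. The other is that the per-protocol set carries the problem into arms 1 and 2. The article says "In sensitivity analyses, the per-protocol set will be analyzed where these patients will be omitted", but the exclusions are still to be defined and nothing says that patients readmitted before the assessment are dropped.

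**Conclusion.** The point holds for index stays in the arm 3 and arm 4 comparisons. As written, rehospitalisations between discharge and enrolment count in controls and tend to keep the stay out of the intervention arms, which favours the intervention.

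The spurious reduction is about 0.7 to 5.7 points for index stays, or 0.4 to 3.5 points over all cases if only the first of 1.6 is affected, against detectable effects of 7 and 6 points. The visit day (3 to 14) and hazard shape (1 to 0.7) are assumptions. So are control follow-up from discharge and a pre-period group without the GP-contact condition. Early deaths in controls may reduce the net size.

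A reader might infer that the whole primary result is biased. The documents do not support that: arms 1 and 2 are recruited before admission and tested first, and are not affected in this way.

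**What to change.** For the arm 3 and 4 comparisons:

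1. Match each enrolled index stay to a control stay whose patient, by the same number of days after discharge, is alive, not in long-term care, not yet readmitted and has had a GP contact. One fixed landmark day with the same conditions in both groups would also do.
2. Start the outcome window at that day in both groups. Ending it at day 90 after discharge keeps it within the planned claims period, which closes 3 months after the intervention phase.
3. Apply the same rule to the pre-period cases of both groups, and state how those cases are chosen.
4. Complete the outcome definition so that the start of the 90 days is explicit for every group.

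Arms 1 and 2 can stay as planned.

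**Cost.** Revised wording and a different control extraction from claims, with no new data collection provided that the claims show the date of the first GP contact after discharge (assumed). Rehospitalisations before the landmark no longer count. From a day-7 landmark with constant hazard (2.0/23 = 9%) to a day-14 landmark with Weibull shape 0.6 (8.2/23 = 36%), that is about 9–36% of index-stay events, so precision falls. The result then applies to patients who reach the GP.

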### Sample size calculation

Since large-scale implementation of the VESPEERA program in a geographical region was intended, the number of participating GPs and hospitals was not restricted. Based on the number of GP-practices who participate in HzV-Care and the number of GP-practices who participate in the PraCMan programme, a number of 115 GP-practices are expected to participate. An estimation of the patient sample size was made using claims-data and several assumptions for hospitalisation rates, rates for planned and unplanned admissions, rates of patients with a high risk of rehospitalisation as well as drop-out rates. Assumptions were made based on analyses of AOK claims-data. Admissions are expected to be planned and unplanned in 50% of the cases, respectively. 56% of planned admissions are made by a GP and therefore can be included in the VESPEERA programme. 40% of planned admissions are cases that are expected to be treated in a participating hospital department. After discharge, we calculated with a 20% drop-out rate for patients who are transferred into a nursing home, who pass away or who do not seek GP contact after discharge. 60% of discharged patients are expected to have a risk of rehospitalisation (HOSPITAL Score indicating an intermediate or high risk for rehospitalisation). Figure 2 gives an overview on the sample sizes in each study arm. Given the estimated sample size, we can estimate the effect size (based on the hospitalisation rates after the intervention) that can be detected. Based on claims-data different numbers of hospitalisations can be expected for each of the intervention groups. The alpha level is set to 5%. The following power considerations are based on chi square tests (to test for group differences) and adjusted for the hierarchical structure of the data. The implemented models in the primary analysis will most likely lead to even higher power values. However, we consider the hierarchical structure of the data with cases nested in patients nested in hospitals or practices, respectively. A relatively high ICC (0.3) can be expected when considering measurements within patients, however the number of cases per patient will be relatively small (approx. 1.6 cases per patient). The clustering by hospitals or practices is taken into account with an expected number of approx. 540 patients per hospital and a presumed ICC of 0.03, which is a realistic value in health services research [20]. Furthermore, we assume a rate of re-hospitalisations of 23% in the control group. With a power of 80%, the following reductions in each of the intervention groups can be shown: For study arm 1 a sample size of 1905 cases can be expected. Hereby, a reduction of approx. 8% (from 23% to approx. 15%) can be shown. The control group will be matched and, therefore, the sample size will be the same. For study arm 2 when compared to the control group, the same reduction is detectable, as the same number of cases can be expected as in study arm 1. In a last step, both the study arms 3 and 4 are compared to the control group using a level of significance of 2.5%. In study arm 3, we expect a sample size of 3266 and, thus, a reduction of approx. 7% (from 23 to 16%) can be shown. In study arm 4, a sample size of 4899 hospitalizations can be expected which allows to show a reduction of approx. 6% (from 23 to 17%).

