### Study population / eligibility criteria

GP-practices within the intervention region have to participate in GP-centred care (*Hausarztzentrierte Versorgung/* HzV). GP-centred care is a programme where, amongst others, the GP has a gate-keeping function (further description of the programme provided by Wensing et al. [13]. Furthermore, Gp-practices have to employ a Care Assistant in General Practice (*Versorgungsassistentin in der Hausarztpraxis/* VERAH). Inclusion criteria for patients are age of 18 years and older, ability to give consent, insurance with the sickness fund AOK Baden-Wurttemberg, participation in GP-centred care according to § 73b SGB V, and at least one hospitalization during the intervention phase. Patients residing in long-term care facilities are excluded from study participation.

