#### Secondary analysis and sensitivity analysis

In addition to the primary analysis, further analyses will be conducted. First, again using the primary outcome but including 12 time points (six before the intervention and six after the intervention (measured month-wise), time trends before and after the intervention will be compared using interrupted time-series-models [27, 28]. Secondary endpoints will be analyzed using the same strategy as used in the primary analysis with adjustments of the models as necessary.

Furthermore, descriptive statistics of all collected data will be performed. Continuous variables will be described using means, standard deviations, median, minimum, maximum, and first and third quartile, separately for each intervention group and the control groups as well as for the total population. Categorical variables will be reported using absolute and relative frequencies.

As claims-based data are used, no missing values are expected to occur, therefore no imputation procedures need to be carried out.

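### The plan expects deaths and other losses after discharge yet declares claims data free of missing values, so early death or insurance exit passes as no rehospitalisation

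*Protocol article*

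**What the plan says.** Four sections of the protocol article bear on this.

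- **Sample size calculation.** For the time once patients have left hospital, "we calculated with a 20% drop-out rate for patients who are transferred into a nursing home, who pass away or who do not seek" contact with the GP. The three reasons share one figure of 20%; no split and no timing are given.
- **Secondary analysis and sensitivity analysis.** "As claims-based data are used, no missing values are expected to occur, therefore no imputation procedures need to be carried out". The sentence carries no qualification.
- **Analysis sets.** The primary analysis is by intention to treat: "patients will be considered in the treatment arm they were assigned to even if, for instance, not all interventions that were planned" for that arm were delivered. In the sensitivity analysis "the per-protocol set will be analyzed where these patients will be omitted". Death, entry into a nursing home and end of insurance are not mentioned.
- **Control group.** For the claims comparison, "to build a patient control group, age, gender, indication group and Charlson Comorbidity Index are used".

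The primary outcome is rehospitalisation for the same indication within 90 days, taken from claims (Outcomes) and modelled as binary by mixed logistic regression (Primary analysis). Under Recruitment, practices enrol "patients with a planned hospital admission" (arms 1 and 2), whereas patients with an unplanned stay (arms 3 and 4) are enrolled in the practice only after discharge. On long-term care, the eligibility section says only this: "Patients residing in long-term care facilities are excluded from study participation". It does not address later entry into care.

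**The concern.** Claims data are complete in one sense: every billed admission of an insured, living person is recorded. They do not supply 90 days of observation for someone who dies or stops being insured on, say, day 20. The plan itself expects deaths after discharge, so the premise that nothing can be missing does not fit its own planning assumptions. The conclusion drawn from that premise, that no handling is needed, has a consequence for a yes/no outcome: truncated follow-up without a readmission becomes a favourable result.

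If such cases are about equally common in both groups, little harm is done. If they are not, a difference in mortality or in insurance turnover is read as a difference in rehospitalisation. The primary comparison is not randomised and the two groups come into being differently, so equality should not be assumed.

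**Working it through.** **1. Are the stated arm sizes before or after the 20%?** Inputs from Sample size calculation: arms 1 and 2 have 1905 cases each, arm 3 has 3266, arm 4 has 4899, and 56% of planned admissions are made by a GP.

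- Arms 3 + 4: 3266 + 4899 = 8165, and 3266 / 8165 = 0.40.
- Planned and unplanned admissions equal, loss taken as division by 1.2, two equal arms: 8165 × 0.56 / 1.2 / 2 = 1905.2. This matches.
- Arms 3 and 4 already reduced, then a 40% share: (8165 / 0.8) × 0.56 / 1.2 × 0.4 = 1905.2. This matches too.
- Loss taken as multiplication by 0.8: 8165 × 0.56 × 0.8 / 2 = 1829. This does not match.

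So 1905 is consistent with a figure net of drop-out. Two different chains give it, however, and Figure 2 is not available, so it stays open whether arms 3 and 4 were reduced as well.

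If 1905 is net and all cases are analysed, arm 1 would hold 1905 × 1.2 = 2286 or 1905 / 0.8 = 2381 cases. Without clustering, 23% versus 15% (two-sided 5%, 80% power) needs 377 per group, so 1905 implies a design effect of 1905 / 377 = 5.05. At that design effect the detectable reduction would be about 7.3 or 7.2 points instead of 8, or power for 8 points would be about 87% to 88%. The stated ICCs and cluster size give a much larger design effect, [1 + 0.6 × 0.3] × [1 + 539 × 0.03] = 20.3. That is a separate matter and is not pursued here.

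**2. Follow one patient through the text.** A patient is discharged, is not readmitted, and dies on day 20. Analysis sets gives no ground for removal. The missing-data sentence treats the value as present. The outcome is binary and no readmission claim exists, so the value is 0, the same as for a patient observed and well for 90 days. The same holds for a patient whose insurance ends on day 20, except that a later readmission may really have occurred and is invisible. Administrative cut-off is not the problem: Data collection and management extends the claims to 3 months after the intervention phase.

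**3. Scale.** Let the rate among fully observed cases be 23% (the plan's control rate) in both groups, with no intervention effect, and let a share d be truncated without readmission and scored 0. Then

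observed rate = 0.23 × (1 − d).

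The plan gives no d, so these values are assumptions:

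| d | observed rate | shift from 23% |
|---|---|---|
| 0% | 23.0% | 0 |
| 5% | 21.85% | 1.15 points |
| 10% | 20.7% | 2.3 points |
| 20% | 18.4% | 4.6 points |

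Only the gap between groups matters: the false difference is 0.23 × (d in one group − d in the other), or 0.23 points per percentage point of gap. The last row would need the whole 20% to be early deaths in one group and none in the other, which nobody should expect. Insurance exit lies outside the 20%, so the table illustrates and does not bound. The difference-in-difference model removes the gap only if it is the same before and after the intervention, and the article does not describe how pre-period cases are assembled.

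**4. Can the groups differ?** Arms 3 and 4 consist of patients who lived to attend the practice after discharge and consented. Arms 1 and 2 consented before admission. The listed matching variables for controls include nothing on survival, nursing-home entry or GP contact. A gap is therefore possible; its sign is not determined.

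**The case against.** The strongest reply is that the 20% is a forecast of case numbers and not a rule for the analysis. It stands between the admission shares and the share expected to qualify for telephone monitoring, which fits an estimate of how many patients reach components E and F. A cautious size allowance and an intention-to-treat set can coexist. This stands.

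A reader might infer more: that the plan contradicts itself on who is analysed, and that arms 1 and 2 lose cases which the controls keep. On that reading, with 20% lost on one side and a rate r among those lost, the retained rate would be (0.23 − 0.20 × r) / 0.80. That gives 18.8% at r = 40%, 21.3% at r = 30%, 23.0% at r = 23% and 26.3% at r = 10%. The documents do not support this reading. No sentence removes these patients from the primary analysis, the 20% is not confined to arms 1 and 2, and every r is invented. Only the per-protocol set is sure to drop patients for undelivered components while controls have no counterpart, and that is a sensitivity analysis.

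It can also be said that the matching variables are not the full rules for controls, that insurance exit is not mentioned anywhere, that the outcome's reference to the outpatient sector may exclude discharges to nursing homes in both groups, and that handling of death usually belongs in the analysis plan. The first three are fair limits on what can be claimed. The last does not dispose of the point: the article does not leave the question open but settles it, on a premise that its own sample size section undercuts.

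**Conclusion.** The point holds in a limited form. The plan expects deaths after discharge and at the same time declares that claims data leave nothing missing and nothing to handle. Taken as written, death or insurance exit within 90 days without a readmission counts as event-free. That coding is the consequence of the text, not a rule it states.

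A resulting bias is possible, because consented intervention patients and claims controls are selected differently, but it is not shown. The only size available is the conversion of 0.23 points per percentage point of gap, which assumes a 23% rate among fully observed cases in both groups and no intervention effect. Loss of cases from the primary analysis of arms 1 and 2 is not established. Whether the arm sizes are gross or net of the 20% is unclear and moves the arm 1 detectable effect by less than one point.

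**What to change.** 1. Replace the no-missing-values sentence. Flag death and end of AOK insurance within 90 days of discharge in the claims of both groups, report their frequency by group and period, and apply one identical rule to cases and controls.
2. Do not count patients who leave the insurer as event-free; without a recorded readmission before leaving, their 90-day outcome is unobserved.
3. Add a sensitivity analysis of rehospitalisation or death within 90 days, with the same model and the same matched groups.
4. State that the 20% concerns delivery of components E and F and is not an exclusion from the intention-to-treat set, and whether the stated arm sizes are before or after it.

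The cost is a few sentences and one extra model, on claims data the insurer should already hold. Keeping patients who did not receive the post-discharge components dilutes the estimated effect somewhat, as intention to treat implies.
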